#### Dimension E—physical activity

The items on physical activity are adapted from the National Health Service's “German Practice Physical Activity Questionnaire” (GPPAQ). The GPPAQ is a short self-report questionnaire that can be used to measure physical performance [44, 51]. Four items were selected for the "screening 45 + " and translated into German. In each case, the amount of time activity per week is recorded in different areas with four gradations from 0 ("2 h or more") to 3 ("not at all").

### Short questionnaire and administrative data

#### Subjective health status

The subjective health status is assessed, according to a recommendation of the World Health Organization (WHO) [52]. There are five answer options from 0 ("very good") to 4 ("very poor"). This item is part of the Minimum European Health Module (MEHM) [45] and is applied in GEDA – German Health Update [53].

#### Previous use of rehabilitation services

The previous use of rehabilitation services may influence application behaviour [54]; therefore the questionnaire asks whether a rehabilitation has already been carried out.

#### Further measurements of work ability

In the short questionnaire the current work ability compared with the lifetime best is measured by the “Work Ability Score” (WAS) [46], the first item from the WAI. The 11-point scale ranges from 0 ("completely unable to work") to 10 ("maximum ability to work"). The subjective prognosis of work ability is assessed with the SPE scale ("subjective prognosis of employability") [27]. Considering the current state of health and work ability, the survey determines whether the current occupation can be carried out until retirement age (0 “sure” to 4 “definitely not”), whether the general work ability is permanently at risk and whether the person is currently considering applying for a disability pension.

#### Work-related data

The German Pension Insurance provides information on voluntary contributions on days with creditable periods due to unemployment in months and the occupational status.

#### Sociodemographic data

Further data regarding gender, age, educational and professional qualifications, subjective socio-economic status as well as primary language spoken in the household will be assessed via the short questionnaire.

### Sample size estimation

The calculation of the sample size is based on a research project that evaluated the psychometric properties, reliability and criterion validity of the “screening 45 + ” [37]. This study revealed a prevalence of 15.8% in total of persons needing prevention or rehabilitation services among insured persons of the German Pension Insurance aged 45 to 60 (*n* = 4,903): 13.0% showed a need for a prevention service and 2.8% a need for a rehabilitation service. Only a few of the persons with a need for prevention or rehabilitation services intend to submit an application. Moog et al. [11] estimate this proportion at 20%. Thus, we expect 3.2% of the participants in the intervention group to apply for a prevention or rehabilitation service after participation in the "check-up 45 + ". We assume an association between the "check-up 45 + " and the application for a German Pension Insurance service if this takes place within 2 months. For the control group, we calculated the proportion based on the statistics from the German Pension Insurance [55]. Consequently, the proportion of insured persons aged 45 to 59 who submit an application for prevention or medical rehabilitation services within two months is estimated at 0.73%.

In order to detect a difference between the intervention and the control group of applications for prevention and medical rehabilitation services, the power calculation (two-sided test, type I error rate: 5%, power: 85%) resulted in a required minimum sample size of *n* = 661 per group. We assume that a proportion of participants cannot be included into the analyses because they do not meet the inclusion criteria. Some inclusion criteria are difficult for the practice staff to verify when recruiting participants, e.g. insurance status. To take into account a possible drop-out rate of 20%, the targeted sample size is increased to *n* = 827 per group. The Consolidated Standards of Reporting Trials (CONSORT) [56] flow diagram is presented in Fig. 2.

**Fig. 2 Fig2:**
[figure not shown]
CONSORT flow diagram of the study

### Recruitment

Before the recruitment phase, the study team visits the GP practices for an one-hour training session on the procedure of the study. The practice staff invite patients who visit the practice for standard care and meet the inclusion criteria (age, insured status) to participate in the study. Study information, consent form and questionnaires are handed out in envelopes for completion. To avoid selection bias, the practice staff is encouraged to address patients who fulfil the inclusion criteria, regardless of their health status and known need for rehabilitation. They should be approached in a neutral way without receiving information about potential prevention or rehabilitation services.

### Allocation

Block randomisation will be performed for each general practice, with the same number of patients per block. Allocation to the intervention or control group is randomised within each block (10 blocks of 10 per practice) to keep the number of case IDs balanced, even if the lists are not finished. The case IDs were generated with R version 4.2.2 and are reproducible. Only the German Pension Insurance is able to link the pseudonyms to the actual persons.

The assignment of the participants included in the study to the intervention or control group is performed randomly, as the practice staff cannot influence the group affiliation of the invited participants during the recruitment process. The practice staff hand out the questionnaires and study documents in sealed, non-transparent envelopes on which the group affiliation is not indicated. The envelopes are only labelled with the questionnaire number (case ID) and are first opened by the participants.

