### Trial design

The “PReHa45” study is a two-arm, pragmatic, 1:1 randomised controlled intervention study (RCT). In GP practices in the German states of Berlin and Brandenburg, patients aged 45–59 years are randomly assigned to an intervention or control group by the practice staff. The intervention group undergoes the "check-up 45 + " in addition to usual care in GP practices, while the control group only receives usual care and completes a general questionnaire on socio-economic and occupational characteristics. The primary criterion for assessing the effectiveness of the "check-up 45 + " is the proportion of applications for prevention and rehabilitation services, determined by administrative data from the individual pension insurance account of the study participants. Practicability, acceptance, and satisfaction with the "check-up 45 + " are examined with semi-structured interviews. The GP practices receive financial compensation for each participant, depending on the effort required. Table 1 shows that according to the nine domains of the PRECIS-2 tool the RCT has a pragmatic approach [38].

**Table 1 Tab1:** PRECIS-2 domain (1 = very explanatory, 5 = very pragmatic)

	**Domain**	**Score**	**Rationale**
1	**Eligibility Criteria**	4	Inclusion and exclusion criteria (especially age and insurance law requirements) largely correspond to legal requirements and the conditions in usual care (exception: patients insured with other GPI agencies, presumably < 5%; maximum age up to standard retirement age would be feasible; sufficient knowledge of German)
2	**Recruitment Path**	5	Recruitment of study participants in the context of usual care visits to about 20 GP practices; possible selection bias because certain patient groups are not addressed (e.g. in acute consultations, but this would presumably also occur in usual care and would therefore not represent a deduction) or certain people tend to refuse participation (e.g. low social status, language barriers, but this would presumably also be comparable in usual care); easy recruitment, but lack of time and staff and high incidence periods of respiratory diseases in winter leads to stagnation in recruitment
3	**Setting**	5	Identical setting to usual care setting: primary care, where patients usually go for advice and treatment; about 20 GP practices in Berlin and Brandenburg (Germany)

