### Treatment

#### Intervention

Participants in the intervention group undergo the “check-up 45 + ”, which includes the completion of the "screening 45 + ". This two-page questionnaire is an assessment to identify existing prevention and rehabilitation needs and measures the five dimensions of work ability, mental well-being, functional ability, coping behaviour and physical activity. These dimensions contain partly adapted questions from established instruments that have been evaluated as useful in practice to predict a risk of work disability or to identify existing limitations in the work ability [37]. It will be handed out with an additional two-page questionnaire covering socio-economic and occupational variables by the practice staff, to be filled out in the waiting room. Immediately afterwards, the "screening 45 + " is evaluated by the practice staff by calculating dimension-specific sum scores and applying predefined thresholds in order to assess a potential prevention or rehabilitation need. Each dimension has a value range from 0 to 12. Depending on the score, there are three possible recommendations: (1) no need for a prevention or rehabilitation service, (2) need for a prevention service, and (3) need for a rehabilitation service, as presented in Table 2. If the practice does not agree with the result (e.g. because of its own previous experience with the patient), the practice is free not to follow the screenings-based recommendation and to give another of the three possible recommendations. Based on the final decision, the following further steps of the “check-up 45 + ” result:

**Table 2 Tab2:** Evaluation of the "screening 45 + "

**Dimension**	**Range**	**Sum score**		**Recommendation**
**Dimension A** *work ability*	0–12	7–12	** → **	Rehabilitation service
		4–6	** → **	Prevention service
		0–3	** → **	No GPI service required
**Dimension B ***mental well-being*	0–12	7–12	** → **	Prevention service
		0–6	** → **	No GPI service required
**Dimension C ***functional ability*	0–12	7–12	** → **	Prevention service
		0–6	** → **	No GPI service required
**Dimension D ***coping behaviour*	0–12	7–12	** → **	Individual measures
		0–6	** → **	No GPI service required
**Dimension E ***physical activity*	0–12	7–12	** → **	Individual measures
		0–6	** → **	No GPI service required

*GPI* German Pension Insurance

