### Blinding

The practice staff are blinded during the recruitment process while inviting patients to the study. Once patients return the completed questionnaires, the practice staff are no longer blinded.

The patients are not aware of their group assignment, as they have no knowledge of the existence of two groups. Unblinding the control group is not intended. Participants in the intervention group are aware of the intervention when they are informed about the result of the "check-up 45 + " after evaluation of the "screening 45 + ". The project coordinators at the German Pension Insurance have no knowledge of the group assignment. The Charité study staff who perform the analyses know the group assignment.

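### With fixed blocks of 10 per practice and staff who learn each arm as questionnaires come back, the procedure does not secure the statement that staff cannot influence group membership

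*Protocol article*

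**What the plan says.** All references are to the protocol article.

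- **Allocation.** "Block randomisation will be performed for each general practice, with the same number of patients per block", set at "10 blocks of 10 per practice". Envelopes are sealed and opaque, carry only the case ID and are first opened by the participant. From this the section concludes that assignment is random, "as the practice staff cannot influence the group affiliation of the invited participants during the recruitment process".
- **Blinding.** Staff are blinded while inviting, but "Once patients return the completed questionnaires, the practice staff are no longer blinded".
- **Intervention.** Practice staff score the screening on the spot. On pack contents, the two-page screening is described thus: "It will be handed out with an additional two-page questionnaire covering socio-economic and occupational variables by the practice staff". Under Control, that arm receives only the two-page socio-economic questionnaire.
- **Recruitment.** Practice staff decide whom to approach. They are encouraged to do so without regard to health status or known rehabilitation need, and in a neutral way.
- **Study setting.** Most practices run the study with one physician and two medical assistants.
- **Trial design.** The study is a "two-arm, pragmatic, 1:1 randomised controlled intervention study (RCT" design.

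**The concern.** Sealed envelopes stop staff from changing an allocation. They do not stop staff from anticipating it and then deciding which patient to approach next. Anticipation needs two things: a restricted sequence, and knowledge of past allocations while recruitment is still running. The article describes both. Because teams are small, the people who learn the past allocations are largely the people who issue the next invitation, and they know many of their patients.

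The primary outcome makes this matter. A patient with known rehabilitation need is more likely to apply whatever the check-up does. If such patients are invited more often when an intervention slot is expected, applications rise in that arm without any effect of the intervention. Events are few: at 661 per group the planning rates imply 661 × 0.0073 = 4.8 control and 661 × 0.032 = 21.2 intervention applications. A handful of steered patients could therefore be visible in the result.

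**Working it through.** **The plan's own figures.** The article gives no figure for predictability. Its sample size reproduces: the continuity-corrected two-proportion formula (two-sided 5%, power 85%) gives 659 per group at 15.8% × 20% = 3.16% against 0.73%, where the article has 661. Then 661 / 0.8 = 826.25, rounded up to 827 per group and 1,654 in total. The present point does not change this.

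**Inputs.** Block size 10 (Allocation). 5:5 within a block, which I infer from the 1:1 design and the stated aim of balance. About 80 patients per practice (Data collection). Control rate 0.73% and 661 per group (Sample size estimation). Fisher's exact test at two-sided 0.05 (Statistical analysis).

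**Step 1: predictability when every earlier packet has been returned.** For a block of 2m with m = 5:
- Expected correct guesses = m + (4^m / C(2m, m) − 1) / 2 = 5 + (1024/252 − 1)/2 = 6.53 of 10, or 65.3%. Perfect concealment gives 50%.
- Expected certain allocations = 2m/(m + 1) = 10/6 = 1.67 of 10, or 16.7%. This is about 276 of 1,654, or about 13 of 80 in a practice.
- Staff need not know the block size to guess above chance. In simulation, a plain running tally of the two arms gives 65.4% correct.

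**Step 2: the same with packets still outstanding** (simulation, 80 patients per practice):

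| Packets outstanding at each invitation | Correct guesses | Certain allocations |
|---|---|---|
| 0 | 65.3% | 16.7% |
| 1 | 60.3% | 6.7% |
| 2 | 58.3% | 2.2% |
| 3 | 56.0% | 0.6% |

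**Step 3: consequence for the primary test.** Assume no effect of the check-up, and that every certain intervention slot, but no other slot, receives a patient with k times the background propensity. The multiplier k is an assumption; the article gives nothing to fix it. With certain share s, the intervention-arm rate is 0.73% × (1 + s(k − 1)). The exact Fisher rejection rate at 661 per group, against 0.73% in the control arm, is:

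| s | k | Intervention-arm rate | False-positive rate |
|---|---|---|---|
| no steering | – | 0.73% | 2.1% |
| 16.7% | 2 | 0.85% | 2.6% |
| 16.7% | 3 | 0.97% | 3.9% |
| 16.7% | 5 | 1.22% | 8.8% |
| 16.7% | 10 | 1.83% | 34% |
| 6.7% | 5 | 0.93% | 3.3% |
| 2.2% | 5 | 0.79% | 2.3% |

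For k = 5, for example: 0.73% × (1 + 0.1667 × 4) = 1.22%. At this low event rate Fisher's test is conservative and starts at 2.1%, which absorbs part of the inflation. The model leaves out steering on slots that are only probable, which would add to these rates.

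**Step 4: would varying the block size alone be enough?** In simulation, the running tally is correct 66.1% of the time with sizes 6/8/10 and about 68% with 4/6/8, against about 65% with fixed 10. Undisclosed varying sizes remove certainty at the end of a block, but they do not reduce guessing from a tally.

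**The case against.** The strongest reply is that the Step 1 figures describe ideal conditions for a guesser, and that the article has safeguards. Staff are told to invite regardless of need and in a neutral way, study staff visit the practices regularly, and several people may recruit in one practice. Study information, consent form and questionnaires travel together in the envelope, so a patient who opens it and declines may use up an ID without staff learning the arm. If 10% or 20% of packets never come back (an assumption), the certain share falls from 16.7% to 9.8% or 5.6%. All of this stands, and it is why 16.7% and 65% are upper bounds. It does not restore the unqualified statement. An encouragement is not a barrier, and guessing stays above 50% even with three packets outstanding.

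Three stronger readings are tempting, and the documents do not support them:
- **That the packs can be told apart by feel.** The intervention pack holds two more questionnaire pages, but both packs also hold study information and a consent form, two pages may be one double-sided sheet, and padding is neither stated nor excluded. This is a possible secondary route only; the block argument does not need it.
- **That payment gives a motive.** The article says "The GP practices receive financial compensation for each participant, depending on the effort required". Compensation for effort is not in itself a reason to steer patients with high need into one arm.
- **That the trial's false-positive rate is about 9%.** That figure needs full immediate knowledge, use of every certain slot and a fivefold propensity. At threefold, or at fivefold with one packet outstanding, the rate stays below the nominal 5%.

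**Conclusion.** The point holds in a limited form. The article's absolute statement is not secured by the procedure it describes. It would go too far to say that the statement is shown to be false or that selection has occurred: staff cannot change what an envelope contains, and nothing in the article shows that anyone has steered patients. The open route is the choice of which patient to invite, and when.

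From the block structure, at most 16.7% of allocations are certain and 65% are guessed correctly. Both fall quickly when packets are outstanding or never returned. The resulting false-positive rate runs from close to its unsteered 2.1% up to 8.8% or 34%, the latter two only with full knowledge and an assumed 5 or 10 times background propensity. These results rest on 5:5 blocks, envelopes used in sequence and steering on certain slots alone. The change is worth making because it is cheap and because, when the article was written, recruitment was under way with practices starting at staggered intervals, so IDs not yet issued could still be protected.

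**What to change.** For unissued IDs and practices still to start:

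1. Regenerate the lists with randomly varying block sizes that are not disclosed to practices. This removes end-of-block certainty only, so it must be combined with the items below.
2. Make the two arms' packs equal in page count and weight, for instance with a filler sheet in the control pack.
3. Issue envelopes strictly in ID order, and log ID and time of issue on the existing study list.
4. In Allocation, replace the absolute statement with a qualified one: staff cannot alter or see an allocation before the envelope is opened, but they learn past allocations during recruitment, and selection is checked for.
5. Report subjective health status and previous use of rehabilitation, which the short questionnaire collects in both arms, by arm and by position within block. A concentration of less healthy patients or previous users in late intervention slots would point to selection.

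The cost is a new randomisation list, a filler page, one extra log entry per envelope and slightly less exact balance within a practice. The sample size is unchanged.

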### Blinding

The practice staff are blinded during the recruitment process while inviting patients to the study. Once patients return the completed questionnaires, the practice staff are no longer blinded.

The patients are not aware of their group assignment, as they have no knowledge of the existence of two groups. Unblinding the control group is not intended. Participants in the intervention group are aware of the intervention when they are informed about the result of the "check-up 45 + " after evaluation of the "screening 45 + ". The project coordinators at the German Pension Insurance have no knowledge of the group assignment. The Charité study staff who perform the analyses know the group assignment.

### Data collection

Primary and secondary outcomes are provided by the German Pension Insurance registers and the questionnaire “screening 45 + ” (Tab. 3). Administrative data can be collected reliably and validly for both groups. The German Pension Insurance transmits these data electronically, encrypted and pseudonymised. This enables a complete recording of the administrative data of all study participants. The data collection by patient questionnaires takes place in the GP practices. The study procedure and the questionnaires were tested and adapted in advance in a pre-test with two practices. The practices start at staggered intervals and aim to recruit about 80 participants per practice. Completed questionnaires are stored in the GP practices. During recruitment, Charité study staff regularly visit GP practices to monitor procedures and collect patient questionnaires. Consent forms and study list are sent by the practices to the German Pension Insurance. If participants withdraw their consent, their collected data will be deleted.

After recruitment is completed, semi-structured interviews will be conducted by telephone or in person to investigate practicability and acceptance of the “check-up 45 + ”. Practice staff, participating patients and employees of the German Pension Insurance involved in the study will be interviewed. The interviews are recorded, transcribed, and analysed anonymously.

### Data management

A detailed data protection concept was developed with the data protection officer of the German Pension Insurance Berlin-Brandenburg, which clarifies the rights of participants as well as the organisational procedures for the collection, processing and storage of data. Pseudonymised administrative data of the participants are transferred from the German Pension Insurance Berlin-Brandenburg and German Federal Pension Insurance to the Charité based on the unique case ID for evaluation after completion of the recruitment process.

Collected questionnaires are scanned and verified at the Charité with the data capture system evasys, to assign the pseudonymised questionnaire data to the corresponding case ID and to export them for the analyses. Data entry and data verification are carried out by trained research assistants. The questionnaires and administrative data can be linked via the unique case ID. The electronic data are stored on an internal server of the Charité. Only the study team has access to the data.

